## 3.3 Study Design

The study will be conducted in the main PHCs of six suburbs in Southwest Harare. Each participating PHC will offer PITC routinely to 6-15 years olds over a two year period, a well as decentralised HIV care including ART initiation. Thus, children who test HIV-positive through PITC will be offered HIV care at the same PHC. At the end of two years of implementation of PITC, an anonymised HIV prevalence survey of 8-17 years olds from randomly selected dwellings in the suburbs served by the study PHCs will be conducted. The prevalence of *undiagnosed* HIV infection in the community following two years of PITC will provide an indication of the effectiveness of primary-care based routine HIV testing in providing high enough coverage of HIV diagnosis in this age-group (>80% of children diagnosed). The survey will also provide data on overall HIV prevalence by age in the considered age-group.

Children who test HIV-positive through PITC at the PHCs and reside in the study suburb where the clinic is located will be recruited into a trial of a VLW-delivered intervention to support to households of HIV-infected children aged 6-15 years. Stratified sampling will be used with randomisation of participants within clinics (1:1) to either a) primary care based HIV care or b) primary care-based HIV care plus treatment support provided by VLWs.

The intervention will be delivered over an eighteen month period, with formative work carried out to inform the design of the intervention. This will consist of qualitative interviews with care-givers of HIV-positive children attending for HIV care and health care providers (nurses, doctors, counsellors and pharmacists) at Harare Central Hospital as well as Community-based Organizations to understand the needs of households with HIV-infected children.

Children testing HIV positive at the PHCs including those recruited into the trial, will be recruited into a clinical cohort study. Data from routine clinic visit (including height, weight, clinical symptoms, incident clinical events and adherence) will be collected. In addition, detailed growth monitoring, lung function testing and a psychosocial assessment (i.e. schooling, guardianship, and disclosure) will be carried out at pre-defined intervals. The HIV care cohort will also provide a platform for immunological studies of slow-progression of HIV infection.

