# STUDY POPULATION

## 4.1 Study Suburbs

Each high-density suburb is served by a main Primary Health Care Clinic (PHC) termed “polyclinic”, which provides acute and antenatal care services to the whole suburb. Six out of the ten high density suburbs in Western Harare were purposively selected on the basis that they have a have a high population of children ≤15 years and the polyclinics do not initiate ART to children in the target age-group. The chosen suburbs comprise approximately 194,885 children aged 6-15 years based on estimates from the Zimbabwe 2002 census.

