## 4.2 HIV diagnosis and care services

Overall HIV prevalence in adults Zimbabwe has been declining and was estimated at 19.2% in 2011, 23.9% in 2010 and 30.6% in 2009 (National AIDS Council Annual Report, 2011). The adult HIV prevalence was estimated 19.1% in the study area during the 2008 DETECTB Household HIV Prevalence survey[[1]](#footnote-2). Estimates from the 2002 National Census indicated that there were approximately 120,182 children aged less than 16 years (mean 20,030, SD 4,409 children per suburb).

In a survey of 6 primary school located in the study suburbs, HIV prevalence among 6-14 year olds was estimated to be 2.7% (Table 4.1). Based on the DETECTB and School HIV Prevalence Survey estimates, the expected HIV prevalence among 6-14 year olds in the study suburbs was estimated to be approximately 14% of the adult prevalence, and thus estimated to range between 1.6% and 3.3%.

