**5.3.1 Randomisation Procedure**

Randomisation will use proportional stratified random sampling using computer generated pseudo –random numbers. The size of each strata will be proportionate to the population size of children aged 6-15 years who are serviced by the clinic (based on Census 2002 data) and are expected to be HIV positive (based on extrapolations from previous surveys in the same study suburbs)

- Stratification will be according to the recruitment clinic (6 clinics)
- The sampling fraction will be 0.175 to ensure that each clinic is allocated study numbers proportional to the expected population of children aged between 6-15 years who test HIV positive (sample which is proportional to size)
- Random allocation to either standard HIV care or to standard care + the support intervention of 1:1 at each clinic will be done, thereby each study number allocated to the clinic will be randomly allocated to either standard HIV care or to standard care + the support intervention
- As the children are recruited into the study, a study number will be allocated consecutively and the appropriate study arm linked to the number.

In the event that the child refuses to participate in the trial and/or is recruited in the cohort only a different study number will be allocated.

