## 11.2 Sample size estimates

### 11.2.1 Individual-randomised trial

A sample of 175 children with newly diagnosed HIV per arm provides 80% power to detect a 45% reduction in proportion of children who miss ≥2 routine appointments in the follow up period in the intervention arm relative to the standard of care arm, given the most likely scenario of 30% missing in the control arm 4, 86, and allow 10% loss to follow-up, assuming a baseline HIV prevalence of 1.8%. The study also has 83% power to detect a 40% difference in proportions who miss ≥2 appointments, assuming that rates in the unexposed arm is 40%.

Studies have shown virological failure rates of 30-70% in older children. 1, 87-88 Assuming that at least 70% of the 175 children per arm with newly diagnosed HIV start ART, we expect 123 children per arm to be on ART. If the treatment failure/death rate among controls is 50%, the study will have 87% power to detect a 40% reduction in this rate. Given that our retention rate into the trial is better than expected, 350 participants will therefore provide adequate power to detect the difference in retention in care between the trial arms, even with the lower sample size.

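### Table 5.1 fixes study numbers per clinic in advance, but the sampling fraction, the row alignment, the clinic count and the age band do not agree, and no rule covers used-up or unused numbers

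*Protocol*

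**What the plan says.** Section 5.3.1 describes randomisation as proportional stratified sampling by clinic. The sampling fraction is 0.175, chosen so that "each clinic is allocated study numbers proportional to the expected population of children aged between 6-15 years who test HIV positive". Each study number allotted to a clinic is randomised 1:1 to an arm, and numbers are issued consecutively as children are recruited. The text gives six clinics as strata. Table 5.1 has seven rows, shows 0.175 in each, and ends in a *Final Sample Size* column that sums to 350.

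Recruitment itself is not described as sampling. Section 3.3 states: "Children who test HIV-positive through PITC at the PHCs and reside in the study suburb where the clinic is located will be recruited". Section 5.3 likewise randomises eligible participants who live in the clinic's suburb.

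The two population totals given from the 2002 census conflict. Section 4.1: "The chosen suburbs comprise approximately 194,885 children aged 6-15 years". Section 4.2: "there were approximately 120,182 children aged less than 16 years".

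The target of 350 comes from 11.2.1: "A sample of 175 children with newly diagnosed HIV per arm provides 80% power to detect a 45% reduction in proportion of children" who miss two or more routine appointments, "given the most likely scenario of 30% missing in the control arm", with an allowance of 10% for loss to follow-up.

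**The concern.** A finite set of pre-assigned numbers per clinic matters only if the clinic can run through it. A child who tests positive after the last number is issued has no number and no arm. Meanwhile another clinic may hold numbers that it never uses. The protocol has no rule for either case, so one would have to be improvised during recruitment.

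The rationing brings no statistical benefit. Allocation is 1:1 within clinic, so the comparison between arms is protected whatever share each clinic contributes.

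If numbers are nevertheless to be rationed, the printed sizes should follow from the stated inputs. They do not. At stake are the total of 350 on which the power rests, the time needed to reach it, and the clarity of the allocation procedure.

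**Working it through.** **1. The plan's power.** Inputs from 11.2.1: 175 per arm, 30% in controls, a 45% reduction (so 16.5%), 10% loss. Significance level and sidedness are not stated there; I assume two-sided 5%. With n = 175 × 0.9 = 157.5 per arm and mean proportion 0.2325, the pooled normal approximation gives

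z = [0.135 × √157.5 − 1.96 × √(2 × 0.2325 × 0.7675)] / √(0.3 × 0.7 + 0.165 × 0.835) = (1.694 − 1.171) / 0.590 = 0.887,

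that is, power of 81.3%. The stated 80% reproduces.

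**2. Table 5.1, row by row.** Population × prevalence reproduces the expected HIV-positive column to within rounding. Its sum is 3,540. The rest follows by multiplication:

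| Clinic | Expected HIV+ | × 0.175 | × 350/3,540 (0.0989) | Printed | Printed / expected |
|---|---|---|---|---|---|
| PHC1 | 375 | 65.6 | 37.1 | 32 | 0.085 |
| PHC2 | 648 | 113.4 | 64.1 | 37 | 0.057 |
| PHC3 | 494 | 86.4 | 48.8 | 64 | 0.130 |
| PHC4 | 790 | 138.2 | 78.1 | 49 | 0.062 |
| PHC5 | 479 | 83.8 | 47.4 | 78 | 0.163 |
| PHC6 | 436 | 76.3 | 43.1 | 47 | 0.108 |
| PHC7 | 318 | 55.6 | 31.4 | 43 | 0.135 |
| Total | 3,540 | 619.5 | 350 | 350 | 0.099 |

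- No printed size equals 0.175 times its row. That fraction gives about 620 in total.
- No printed size equals its own row's proportional share of 350. Every one equals the share of the row above, and PHC1 carries PHC7's. The rounded shares sum to 349, which may explain why PHC7's 31.4 appears as 32.
- The fraction actually applied runs from 0.057 to 0.163, so the column is not proportional to size.

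**3. Six clinics or seven.** Rows PHC1-6 hold 32 + 37 + 64 + 49 + 78 + 47 = 307 numbers. With 307 × 0.9 / 2 = 138.15 per arm, the formula in step 1 gives 76.0%. Only all seven rows reach 350.

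**4. Census counts.** The populations of PHC1-6 sum to 120,182, with mean 20,030 and SD 4,409. These are exactly the figures that 4.2 gives for children under 16, yet 5.3.1 uses the series as ages 6-15. The 194,885 aged 6-15 in 4.1 is 194,885 / 120,182 = 1.62 times that count, although ages 6-15 lie within under-16. The 194,885 does not enter Table 5.1.

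**5. If the printed sizes act as caps.** This is conditional, because the protocol does not state a stop. I assume that eligible children arise in proportion to the expected column and that each clinic enrols the smaller of its arrivals and its printed size.

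| Eligible children | Enrolled, counts exactly as forecast | Enrolled on average, Poisson counts | Power (Poisson average, 10% loss) |
|---|---|---|---|
| 350 | 289 | 287 | 73% |
| 437.5 | 325 | 321 | 78% |
| 525 | 343 | 340 | 80% |
| 619.5 | 350 | 348 | 81% |

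At 350 eligible children the loss comes from PHC1, PHC2 and PHC4: (37.1 − 32) + (64.1 − 37) + (78.1 − 49) = 61.3 children without a number, to rounding.

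**The case against.** The best defence is that Table 5.1 is a forecast. Its caption speaks of an expected size by suburb, and 5.3.1 nowhere says that a clinic stops when its numbers run out. Trial SOPs are listed in Appendix 18.4 and may deal with the point. Section 4.5 also foresees children testing positive after trial enrolment is complete, so the plan expects more positives than trial places. With a surplus of the size that 0.175 implies, every printed allotment fills. All of this stands, and it is why a shortfall is a risk and not a prediction.

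A reader might go further in three ways that the documents do not support.

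- *That the contradictory census totals make some clinics run out.* Table 5.1 uses one series only, and an error common to all clinics leaves the shares unchanged. The contradiction needs reconciling but does not drive the allotment.
- *That 350 will be missed.* The column sums to 350, no hard cap is written, and the protocol gives no diagnoses by clinic from which to judge.
- *That 11.2.1 admits a shortfall when it says "even with the lower sample size".* The phrase refers to the 350 on which the power is calculated and is tied to better retention than expected. It says nothing about clinic allotments.

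None of this repairs the table. Even as a forecast, it has the wrong fraction, displaced rows and an unclear number of clinics.

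**Conclusion.** The point holds as an internal error with a conditional consequence. Arithmetic on the protocol's own figures shows that 0.175 should be about 0.099 if the total is 350, that all seven printed sizes sit one row too low, that six clinics account for only 307 numbers, and that one population series carries two age labels. These results need no assumption beyond the printed table.

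The effect on the trial depends on how the numbers are used. If the printed sizes bind and 350 eligible children arise as forecast, about 287 enrol and power falls from 81% to about 73%, or recruitment takes longer. If about 620 arise, the loss is negligible. These power figures assume a two-sided 5% test and arrivals in proportion to the expected column. The comparison between arms is not biased by the displaced rows, because allocation is 1:1 within each clinic.

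**What to change.** - In 5.3.1, remove the 0.175 fraction and the per-clinic totals as limits on allocation. Prepare for each clinic a concealed 1:1 list longer than its expected number, for example in permuted blocks. Recruit consecutively at every clinic and stop when 350 have been randomised overall. No rule for exhausted or unused numbers is then needed.
- Keep Table 5.1 only as a forecast, with a fraction of about 0.099, rows realigned (37, 64, 49, 78, 47, 43 and 31 or 32), and one number of clinics used in the table and throughout the text.
- Reconcile 4.1, 4.2 and Table 5.1 to one census count for one stated age band.

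The cost is list generation and wording. If recruitment has begun, existing lists should be extended rather than replaced. The one downside is that the clinic mix will follow actual diagnoses instead of the census, which does not affect the validity of the within-clinic comparison.

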**Table 5.1: Expected sample size by suburb**

| **Stratum** | **Population Size**  **(2002 Census)** | **Estimated HIV Prevalence** | **Population Size (Expected HIV+ve)** | **Sampling Fraction** | **Final Sample Size** |
| --- | --- | --- | --- | --- | --- |
| PHC1 | 14519 | 2.58 | 375 | 0.175 | 32 |
| PHC2 | 24695 | 2.62 | 648 | 0.175 | 37 |
| PHC3 | 23036 | 2.15 | 494 | 0.175 | 64 |
| PHC4 | 23789 | 3.32 | 790 | 0.175 | 49 |
| PHC5 | 18556 | 2.58 | 479 | 0.175 | 78 |
| PHC6 | 15587 | 2.80 | 436 | 0.175 | 47 |
| PHC7 | 19203 | 1.66 | 318 | 0.175 | 43 |

## 5.4 Formative work

Formative research will consist of a short qualitative study to explore key local facilitators and barriers experienced by primary caregivers of HIV+ children aged 6-15 years in seeking to optimise their access to, retention in, and adherence to HIV treatment and care. It will provide data specifically for the design of the community-based adherence support intervention, and will build on existing research conducted in Zimbabwe on the contextual and social determinants of treatment adherence among paediatric HIV patients. The research question is "What local social and contextual factors enable children’s retention in HIV care and how might these be strengthened?"

The objectives of the formative research are to:

1. Describe HIV+ children’s caregivers’ perspectives on their experiences of caring for children requiring chronic HIV care, including challenges confronted related to maintaining appointments, ensuring treatment adherence, and supporting well-being more generally
2. Identify the specific material, symbolic and relational factors that enable HIV-infected children’s retention in care, and the local norms and social networks that either facilitate or hinder these factors.
3. Elicit the health providers’ views on how children, caregivers, other family members and communities engage with care, and their suggestions for how support can be provided at community level but remain linked to facilities.
4. Identify, map and obtain information on existing community-based initiatives that provide adherence support or similar outreach to families of HIV+ children.

Fieldwork will be conducted in the catchment area of Harare Hospital and take place in October 2012. Data will be collected from three types of respondents: (1) Harare Hospital health care providers, including those involved in clinical care and counselling/outreach; (2) Primary caregivers of HIV+ children aged 6-15 who have been enrolled in HIV care at Harare Hospital for at least 6 months; and (3) representatives or key informants from any existing community based organisations (CBO) engaged in providing adherence support or related services (such as distribution of food supplements, or home based care providers).

First, focus group discussions will be held with health care providers (both clinical and not), to identify the main issues relating to current provision of care to HIV+ children, and their perceptions of the unique challenges faced by the children’s primary caregivers, extended family members, and wider communities. The group discussions will also introduce the study to providers and familiarise them with the study fieldworkers, who will be collecting data regularly at the hospital.

Caregivers will then be recruited into the study for semi-structured interviews. They will be sampled to reflect diversity according to their relationship to the child(ren) for whom they care, and background characteristics including age, sex, and residence. Interviews will be conducted at the hospital and will address caregivers’ experiences of supporting HIV+ children in health-seeking, diagnosis, disclosure (if applicable), attending regular appointments, undertaking medical tests, taking medication, and positive living more broadly (mitigation of stigma, relationships at school, nutrition, psychosocial care, etc.)

Both providers and caregivers will be asked about existing community-based support programmes such as food supplementation, support groups, home based care visits, etc., and if any of these prove relevant, they will be mapped according to location, and services provided. Key informants will then be sought from each organisation and invited to a brief interview to determine what adherence support mechanisms already function in local communities, which appear to be successful, and why.

Analysis will use thematic content analysis and be driven by conceptual frameworks already developed in research conducted on barriers and facilitators to retention in care and treatment adherence. In particular, enabling conditions within family, community, and institutional structures will be extracted from the data, as well as any suggestions for what might work to increase sustained participation in care; these will be analysed with reference to evidence from the literature on the feasibility and effectiveness of different adherence support intervention components.

# HOUSEHOLD-LEVEL VLW SUPPORT

Community-based adherence support will be provided to families enrolled in the ZENITH trial by Voluntary Lay Workers (VLW) who will be recruited and trained to offer psychosocial counselling, practical advice, and links to appropriate referrals. The exact structure of the intervention, including guidelines and protocols specifying the nature and frequency of activities provided by VLWs, will be determined following the formative research described in Section 5.4, which will identify locally important facilitators and barriers experienced by the primary caregivers of HIV+ children. However, the LHW programme will centre around a series of home visits to (1) assess each enrolled family’s circumstances and needs; (2) identify feasible measures that caregivers might put in place to maximise engagement with care; (3) offer both general support and tailored assistance, following standardised guidelines; and (4) refer families to locally available organisations offering additional support services. Finally, LHW will serve as a link to the HIV treatment services by reminding caregivers of scheduled appointments, and following-up with clinic staff to check families’ attendance and identify emerging concerns that could lead to attrition from care.

## 6.1 Recruitment and training of LHW

Existing research on different models of community-based adherence support suggest that formalised management procedures, transparent employment policy, and clear terms of reference all contribute to job satisfaction and sustainability in lay health worker programmes. We will thus work through existing community based organisations to identify suitable candidates.

Eligibility criteria will include residence in the local community for at least 5 years, functionally literate (able to read and fill in rudimentary record-keeping forms, basic comprehension of literature such as health pamphlets circulated to clinic patients), willingness to travel on foot between households and regularly visit the local clinic, and ability to demonstrate experience of nurturing others (including caring for their own or others’ children, sick or elderly family members, or previous work experience in a caring capacity i.e. nurse, midwife, social worker). LHW workers will be contracted on a probationary period for two months (including the first two weeks of training) and their contract confirmed after a “refresher” workshop held at the end of the probationary period.

Training will be conducted over two weeks, followed by a further two weeks of intensive on-the-job supervision. Training will cover basic information related to HIV transmission, prevention, treatment regimens, care needs, and orientate LHW on common challenges families face in initiating treatment and sustaining adherence and retention in care. It will emphasise the importance of a family-centred strength-based case management approach, and explain the protocols developed for each scheduled home visit. The LHW will be taught how to address each family’s needs, provide information and support related to treatment adherence, including managing side-effects, encourage testing among other family members, encourage testing among other family member, and facilitate discussion around age-appropriate disclosure of HIV status to the child, and to other family and community members, where feasible.

Training will involve a mix of familiarisation with project guidelines, illustration through examples and case studies, role-plays, and participatory activities. During the intensive 2-week supervision period following the training, each LHW will be “shadowed” for a day as they conduct visits and contacted by phone at the end of each day to debrief and discuss any questions or uncertainties. Finally, after two months, a 2-day refresher workshop will be held so that LHW can discuss concerns, share initial experiences and problems, and work together as a team to seek solutions to any challenges confronted in their work. Additional 1-day workshops will be held every 6-9 months in order to maintain lesson-learning across the programme, build team unity, address any difficulties emerging during the programme, and ensure LHW receive up-to-date information and guidance related to the treatment component of the intervention.

